### Study limitations, data biases, and mitigation strategies

2.9

Despite being an open-label study, the potential bias introduced is minimal, as both the maneuvers and outcome evaluation are performed by the same person. The primary outcome (resolution of nystagmus) is assessed objectively through videonystagmography, which does not require interpretation by the evaluator.

There is a risk of patient dropout during the eight-week period of Brandt-Daroff exercises prior to the personalized maneuver. To mitigate this risk, patient adherence will be closely monitored and encouraged with reminders and follow-ups.

Since patients will be recruited from three different hospitals, there may be diagnostic biases depending on the evaluator. However, all intervention maneuvers (both personalized and conventional) will be conducted at a single center, where a diagnostic reevaluation will be performed prior to intervention to confirm that the BPPV remains unresolved and exclusively affects the posterior canal.

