### Study design

2.1

This is an experimental, multicenter, open-label, randomized study (using balanced block randomization) with two parallel arms. The study targets patients with a definitive diagnosis of refractory posterior semicircular canal BPPV (BPPVp).

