### Data collection

2.6

Even if intermediate visits are necessary, the following study visits will be conducted according to the protocol (with data recording):

Visit 1 (eight weeks after inclusion):

The Dix-Hallpike Test (DHT) will be performed with videonystagmographic recording. If positive:In the control group, the conventional Epley maneuver will be repeated using a mechanized chair.In the study group, a personalized Epley maneuver will be performed using a mechanized chair.

Visit 2 (ten weeks after inclusion):

The DHT will be repeated with videonystagmographic recording. If positive:In the control group, the conventional Epley maneuver will be repeated using a mechanized chair.In the study group, the personalized Epley maneuver will be repeated using a mechanized chair.These maneuvers (conventional for the control group and personalized for the study group) will be repeated every two weeks until resolution of symptoms (or up to a maximum of 8 repetitions).

Visit 3 (Six months after inclusion):

The following variables will be recorded:Dix-Hallpike Test (DHT) results (negative or positive).Dizziness Handicap Inventory (DHI) score.Number of consultations required for resolution.

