### Data analysis

2.8

Demographic data and patient characteristics will be described globally and by relevant covariables.

Continuous outcomes will be summarized using mean, median, standard deviation (SD), and interquartile range (P25, P75). For categorical outcomes, the number and percentage of patients in each category will be reported. Statistical analyses will be based on the full analysis set (FAS), which includes all randomized participants who provided informed consent and met all inclusion criteria without any exclusion criteria. The analysis will follow the intention-to-treat principle.

The key outcome variables of interest are:

Resolution of nystagmus (yes vs. no), which is the primary outcome.Resolution of symptoms (yes vs. no).DHI score (minimum: 0; maximum: 100) at inclusion and 6 months after inclusion.Number of consultations required until resolution.

Covariables of interest include:

Baseline patient characteristics:Sex.Age at inclusion.Nystagmus latency period during the Dix-Hallpike Test (in seconds).Nystagmus duration during the Dix-Hallpike Test (in seconds).Mean slow-phase velocity of the vertical component of nystagmus during the Dix-Hallpike Test (in degrees/s).Associated risk factors:Duration of symptoms.Etiology.Adherence to the intervention (direct observation by the investigator in both intervention arms).

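### Having the same unmasked person treat and assess is a possible source of detection bias, not a reason to call bias minimal; this design allows masking that the article does not describe

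*Protocol article*

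**What the plan says.** Section 2.1 declares the design: "This is an experimental, multicenter, open-label, randomized study (using balanced block randomization) with two parallel arms". Section 2.9 then gives two reasons why the lack of masking matters little.

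- First, "the potential bias introduced is minimal, as both the maneuvers and outcome evaluation are performed by the same person".
- Second, the primary outcome "is assessed objectively through videonystagmography, which does not require interpretation by the evaluator".

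The primary outcome in Section 2.8 is a binary call: "Resolution of nystagmus (yes vs. no), which is the primary outcome". The other key outcomes there are symptom resolution (yes or no), the DHI score and the number of consultations until resolution. Section 2.3 has patients complete the DHI themselves.

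For Visit 1, Section 2.6 states: "The Dix-Hallpike Test (DHT) will be performed with videonystagmographic recording". Visit 2 repeats this. The Visit 3 list at six months gives "Dix-Hallpike Test (DHT) results (negative or positive") and does not mention a recording.

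Sections 2.4 and 2.6 give both arms eight weeks of home exercises, an MRI, the same visits and an Epley maneuver in a mechanized chair. For the controls: "In the control group, the conventional Epley maneuver will be repeated using a mechanized chair". The study arm has the personalized version. Section 2.9 places all maneuvers at a single center. The article describes no masking of participants, of the assessor or of whoever classes the recordings.

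**The concern.** The first reason in Section 2.9 runs the wrong way. A single rater removes differences between raters. It does not remove the effect of that rater's expectations, and here the rater knows the arm and has just delivered the maneuver under test. If doubtful cases are read more favorably in one arm, the difference between arms shifts and randomization gives no protection.

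The second reason is a real safeguard, but it concerns nystagmus alone. Three outcomes lie outside it:

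- Symptom resolution depends on what a participant who may know the arm reports to an assessor who does know it.
- The DHI is completed by participants who may know their arm.
- The consultation count depends on when resolution is declared. Under Section 2.6 maneuvers are repeated every two weeks until symptoms resolve, up to eight times, so the same unmasked judgement feeds into it.

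At stake are the credibility of these secondary comparisons and, to whatever extent classing a recording leaves room for judgement, of the primary comparison too.

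**Working it through.** **1. Which outcome each defence covers**

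| Outcome (Section 2.8) | Same-person argument | Videonystagmography argument |
|---|---|---|
| Resolution of nystagmus (primary) | Reduces rater variation only | Covers it, as far as no judgement is needed |
| Resolution of symptoms | Reduces rater variation only | Does not cover it |
| DHI | Not relevant (self-completed) | Does not cover it |
| Consultations until resolution | Reduces rater variation only | Does not cover it |

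No cell in the first column removes a difference between arms that comes from knowing the allocation.

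**2. Is masking possible?** Common to both arms are the home exercises, an MRI (Section 2.4), the visit schedule and an Epley maneuver in a mechanized chair (Section 2.6), and the single treating center (Section 2.9). The planned difference is the angle setting. Participants can therefore be kept unaware of it. The operator who sets the angles probably cannot.

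**3. The plan's own figure.** Section 2.10 assumes 25% against 75%, two-sided alpha 0.05 and power 95%, and gives 23 per arm. With pooled variance under the null:

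n = [1.960·√(2·0.5·0.5) + 1.645·√(0.25·0.75 + 0.75·0.25)]² / 0.50² = (1.386 + 1.007)² / 0.25 = 22.9, rounded up to 23.

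The figure reproduces (power at 23 per arm is 95.1%). Masking does not enter the formula, so the number stands.

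**4. Illustration of size.** Inputs from Section 2.10 are the 25% control rate and 23 per arm (27 with the dropout allowance). Two inputs are assumptions: there is no true effect, so 25% applies in both arms, and a share m of unresolved study-arm patients is called resolved, with no misreading among controls. The apparent study-arm rate is

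p = 0.25 + 0.75·m.

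The probability of a two-sided p-value below 0.05 is the sum of exact binomial probabilities over all rejecting tables.

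| m | Apparent study-arm rate | Chi-square, n=23 | Fisher, n=23 | Chi-square, n=27 | Fisher, n=27 |
|---|---|---|---|---|---|
| 0 | 25.0% | 5.2% | 2.5% | 5.6% | 2.2% |
| 5% | 28.75% | 6.0% | 3.1% | 6.7% | 3.0% |
| 10% | 32.5% | 8.6% | 4.8% | 10.0% | 5.2% |
| 15% | 36.25% | 12.9% | 7.8% | 15.3% | 9.0% |
| 20% | 40.0% | 18.9% | 12.1% | 22.4% | 14.6% |

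In patients, m = 15% at 23 per arm is 23 × 0.75 × 0.15 = 2.6, that is, two or three. Almost all of the excess favors the study arm: by chi-square, the chance of a significant result in that direction rises from 2.6% at m = 0 to 12.6% at m = 15%.

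**The case against.** The strongest reply is that the primary outcome is instrumental. The Introduction says videonystagmography quantifies intensity and duration and determines direction, Section 2.5 lists latency, duration and slow-phase velocity as variables, and Section 2.9 says no interpretation is needed. If that is so, m is near 0 for the primary outcome and the m = 0 row applies. No passage says that reading a trace takes judgement. This stands as a limit on the concern: the primary outcome is less exposed than the others.

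Four stronger readings are tempting, and the documents do not support them.

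- *That the trial's type I error is 13% to 15%.* That follows only from an assumed 15% misreading in one arm and one direction, combined with a chi-square test the article does not name. Fisher's test under the same assumption gives 7.8% and 9.0%.
- *That resolution is left undefined.* The article states no threshold, but it condenses a fuller protocol that may contain one.
- *That Visit 3 is not recorded.* This would be an inference from silence. The Visit 3 list omits recording, but Section 2.9 describes the primary outcome as assessed by videonystagmography without limiting this to certain visits. The wording is unclear rather than wrong.
- *That colleagues at two other hospitals can read the traces.* The article does not say that the treating center is one of the three recruiting hospitals, or that readers are available elsewhere.

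It is also fair to say that the open-label status is openly declared, and that the study period in Section 2.2 began in January 2024. Some participants may already know their arm.

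None of this rescues the same-person argument or extends the videonystagmography argument to the other three outcomes.

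**Conclusion.** The point holds in this form. The first rationale in Section 2.9 is wrong as written: a single unmasked person who treats and assesses may reduce rater variability but creates a risk of detection bias between arms. The second rationale lowers that risk for the primary outcome only. Symptom resolution, the DHI and the consultation count remain unprotected, although participants can be masked at little cost.

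The size cannot be fixed from the documents. With 0 to 20% misreading confined to the study arm, type I error at 23 per arm runs from 5.2% to 18.9% by chi-square and from 2.5% to 12.1% by Fisher's exact test. The lower end applies if the recording truly needs no judgement. These figures illustrate sensitivity and do not estimate this trial's error rate. The conclusion about the rationale, and about the three unprotected outcomes, does not depend on them.

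**What to change.** 1. Do not tell participants whether the chair uses standard or personalized angles, and word the information sheet accordingly. If some already know their arm, record this and report the patient-reported outcomes by masking status. If masking is judged impracticable, say why in Section 2.9.
2. Class nystagmus resolution for the analysis from coded videonystagmography files with arm labels removed, by a fixed rule on the slow-phase velocity and duration already listed in Section 2.5. If the full protocol holds such a rule, refer to it. A fixed rule means no additional reader is required. Confirm in Section 2.6 that Visit 3 is recorded in the same way as Visits 1 and 2.
3. Delete the same-person rationale from Section 2.9. State instead that the operator is unmasked, that videonystagmography protects the primary outcome only, and that a risk remains for symptom resolution, the DHI and the consultation count.

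The cost is protocol and consent wording, the coding of files already recorded and, if not already planned, a recording at Visit 3. The sample size stays at 23 per arm (54 in total with the dropout allowance). Participants who already know their arm cannot be masked afterwards, so the trial may end with a mixture of masked and unmasked participants, which has to be reported.

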### Sample size and calculation methodology

2.10

To estimate the sample size, we assume that approximately 25% of patients with refractory BPPVp may be cured through repeated maneuvers or Brandt-Daroff exercises (control group). A significant difference of 50% in the study group (i.e., a 75% efficacy rate for symptom resolution) is considered clinically meaningful. With a 95% confidence level (1-*α*) and 95% statistical power for a two-tailed hypothesis test, a sample size of 23 participants per arm is required. Thus, the estimated total sample size is 46 individuals, increased to 54 (27 per group) to account for a 15% anticipated dropout rate.

## Discussion

3

Previous studies have compared the effectiveness of manual canalith repositioning maneuvers (CRMs) against the TRV chair in patients diagnosed with BPPV, focusing on treatment success, quality of life, and recurrence rates. However, while mechanical chairs can be useful, especially in specific subpopulations (elderly patients with mobility limitations), they do not significantly outperform manual maneuvers (23).

Another recent study has shown that TRV chair could be useful in diagnosis for complex BPPV cases, patients with impaired cooperation or as a second opinion diagnostic tool for treatment-resistant BPPV (24).

Specifically, a systemic review focused on the use of multi-axial repositioning chairs (25), like the TRV chair and Epley Omniax Rotator, in the diagnosis and treatment of BPPV have found:

Symptom relief was high, with treatment success rates between 68 and 100%.Recurrence rates ranged from 11 to 27.9%.Multi-axial chairs were found effective, particularly for patients who could not undergo manual repositioning or had rarer forms of BPPV.Minor adverse effects like nausea and claustrophobia were reported in some cases.

So, the conclusion drawn was that Repositioning chairs appear safe and effective for managing BPPV, including difficult cases. However, the lack of RCTs limits the ability to compare their effectiveness directly with traditional manual methods.

Recently, a study has aimed to investigate whether patients with very refractory BPPV could be effectively treated using a mechanical rotational chair (MRC) tailored to individual inner ear anatomy (26). The MRC allows for individualized adjustments based on specific angles of the semicircular canals (SCC), and the inner ear anatomy was evaluated using CT scans. Complete remission of both symptoms and objective findings was achieved in 21.4% of patients, and subjective relief was reported in 42.9% of patients. Noteworthy, the study found significant differences in SCC angles from standard anatomical assumptions, which may explain the refractoriness to traditional treatments.

Our current study protocol is based on MRI imaging (to avoid x-ray) to measure individual SCC-angles and latter prepare individual treatments adjustable with the MRC.

To the best of our knowledge, this is the first study evaluating the possibility of resolving refractory BPPVp through the customization of maneuver angles with the application of CFD techniques. The study is relevant as it aims to adapt existing technologies (MRI, CFD techniques, and the TRV mechanized chair) to achieve cost savings and improve the quality of life for these patients.

In future studies, we plan to personalize the resting time based on specific nystagmus characteristics or patient conditions. Additionally, parameters such as rotation velocity may be explored to further optimize certain maneuvers.

Also, future studies should integrate experimental validation with patient-specific vestibular assessments.

The use of CFD modeling based on MRI reconstructions represents a novel step toward personalized medicine in vestibular disorders. While this study focuses on refractory BPPV, the approach could be extended to other vestibular conditions where individualized anatomical variability plays a role in treatment efficacy. Future studies should investigate the integration of these methods to optimize vestibular disorder management and enhance treatment outcomes across different patient populations.

Additionally, the project will have an incentivizing effect on the institution: the application of CFD techniques to the study of endolymphatic fluid movement opens the door to new research lines aimed at optimizing diagnostic tests for vestibular function.

## Ethics and dissemination

4

The data will be collected in a specially designed database. There will be periodic data quality controls. The PI will monitor the study and ensure that the data are authentic, accurate and complete, and that the subjects’ safety and rights are protected.

The protocol has been approved by the Independent Ethics Committee of Galicia (protocol 2022/143).

The study will be carried out in compliance with current ethical standards and in accordance with the principles established in the Declaration of Helsinki, including all applicable amendments set forth by the ICH guidelines for Good Clinical Practice. Similarly, it will be ensured that all individuals involved in the project respect the confidentiality and security of any information related to the study subjects, in accordance with the provisions of Law 3/2018 on Personal Data Protection and Guarantee of Digital Rights. Upon completion of the study, the results will be disseminated and published, taking into account that the data will be anonymized, coded, and de-identified in order to deposit them in the designated repositories and enable their use in future research.
